## Abstract

**Background:**

Over the past two decades, the population of Malaysia has grown rapidly and the prevalence of diabetes mellitus in Malaysia has dramatically increased, along with the frequency of obesity, hyperlipidaemia and hypertension. Early-life influences play an important role in the development of non-communicable diseases. Indeed, maternal lifestyle and conditions such as gestational diabetes mellitus or obesity can affect the risk of diabetes in the next generation. Lifestyle changes can help to prevent the development of type 2 diabetes mellitus. This is a protocol for an unblinded, community-based, randomised controlled trial in two arms to evaluate the efficacy of a complex behavioural change intervention, combining motivational interviewing provided by a community health promoter and access to a habit formation mobile application, among young Malaysian women and their spouses prior to pregnancy.

**Method/design:**

Eligible subjects will be Malaysian women in the age group 20 to 39 years, who are nulliparous, not diagnosed with diabetes and own a smartphone. With an alpha-value of 0.05, a statistical power of 90 %, 264 subjects will need to complete the study. Subjects with their spouses will be randomised to either the intervention or the control arm for an 8-month period. The primary endpoint is change in waist circumference from baseline to end of intervention period and secondary endpoints are changes in anthropometric parameters, biochemical parameters, change in health literacy level, dietary habits, physical activity and stress level. Primary endpoint and the continuous secondary endpoints will be analysed in a linear regression model, whereas secondary endpoints on an ordinal scale will be analysed by using the chi-squared test. A multivariate linear model for the primary endpoint will be undertaken to account for potential confounders. This study has been approved by the Medical Research and Ethics Committee of the Ministry of Health Malaysia (protocol number: NMRR-14-904-21963) on 21 September 2015.

**Discussion:**

This study protocol describes the first community-based randomised controlled trial, to examine the efficacy of a complex intervention in improving the pre-pregnancy health of young Malaysian women and their spouses. Results from this trial will contribute to improve policy and practices regarding complex behavioural change interventions to prevent diabetes in the pre-conception period in Malaysia and other low- and middle-income country settings.

**Trial registration:**

This trial is registered with ClinicalTrials.gov (www.clinicaltrials.gov) on 30 November 2015, Identifier: NCT02617693.

**Electronic supplementary material:**

The online version of this article (doi:10.1186/s13063-016-1345-x) contains supplementary material, which is available to authorized users.

## Background

Diabetes mellitus (DM) is one of the most common non-communicable diseases (NCDs) across the world. Today 387 million people are living with diabetes whereas 46.3 % remain undiagnosed. The prevalence of DM is expected to increase to 53 % by 2035 [1]. DM is an important public health concern in Malaysia. Over the past two decades, the population of Malaysia has grown rapidly and the prevalence of DM in Malaysia has increased dramatically, along with the prevalence of obesity, hyperlipidaemia and hypertension. The National Health and Morbidity Survey (NHMS) 2015 estimated the prevalence of DM in adults 18 years old and over was 11.6 % in 2006 and 17.5 % in 2015 [2]. The prevalence of DM has almost tripled over the past two decades in the younger generations (20–39 years old) [2, 3].

There is a body of evidence showing that lifestyle changes, such as achieving a healthy body weight, can help to prevent the development of type 2 diabetes mellitus (T2DM) [4–6]. Complex behavioural change interventions, or lifestyle intervention trials, have also moved in the past decade from targeting high-risk to low-risk populations and interventions have also been targeted earlier in the life course [7–9]. The use of new communication technologies, such as computer-based interventions, and empowerment techniques such as goal setting, have been found to be helpful and eventually more effective than other interventions on weight loss and self-management of T2DM [10–13]. Lifestyle interventions seek to delay or halt the development of T2DM and achieve, e.g. a healthy body weight. Goal setting requires a coordinated team effort that involves the person at risk in the decision-making process. Evidence demonstrates that structured, intensive lifestyle programmes involving participant education, individualised counselling, reduced dietary energy and fat intake, regular physical activity, and frequent participant contact are necessary to produce long-term weight loss of 5–7 % [14].

The Developmental Origins of Health and Disease (DOHaD) concept describes how during early life (at conception, and/or during foetal life, infancy and early childhood), the environment induces changes in development that have a long-term impact on later health and disease risk [15]. Early-life influences play an important role in the development of NCDs, and maternal lifestyle and conditions such as gestational diabetes mellitus (GDM) or obesity can affect the risk of diabetes in the next generation [16, 17]. Besides complications of pregnancy such as GDM, hypertension, and preeclampsia that directly affect the pregnancy outcome, the mother’s health during pregnancy affects her child’s risk of becoming overweight or obese. If the mother makes lifestyle choices that lead to unbalanced nutrition, obesity, stress, smoking and others, her child is more vulnerable to diabetes and other NCDs [18]. Children born to mothers with GDM have a four to eight times higher risk of obesity, glucose intolerance and T2DM in adolescence or young adulthood [19].

The Jom Mama project has been designed to develop an intervention which responds to this rising public health challenge, focusing on young Malaysian women and their spouses. The overall aim of the Jom Mama project is to demonstrate whether a complex behavioural change intervention will change markers of health in the young Malaysian woman in the pre-conception period, before evaluating whether the intervention affects the pregnancy course and the neonate susceptibility to obesity and diabetes. The Jom Mama project is a public-private partnership between the Ministry of Health (MoH), Malaysia; the University of Southampton, UK; the University of Witwatersrand, South Africa; the Steno Diabetes Centre, Denmark; and Novo Nordisk, Denmark. The project was initiated in 2012 and is following Intervention Mapping guidelines, which is a systematic framework to develop health promotion programmes [20]. The Jom Mama project is conducted in three phases; phase 1: to develop knowledge on the lifestyle of young couples in Malaysia and identify the barriers and facilitators of health [18, 21]; phase 2: to develop intervention matrices and develop an intervention package based on the outcome from phase 1; and phase 3: to implement and evaluate the developed intervention package in a randomised control trial (RCT). In this paper we will present the study protocol for an unblinded, community-based, RCT with two arms to evaluate the complex behavioural change intervention developed in phase 2 of the Jom Mama project.

## Methods/design

### Aim

The primary objective of the trial is to evaluate the efficacy of a complex behavioural change intervention combining behaviour change counselling provided by community health promoters (CHPs) and utilisation of an E-health platform to enhance women’s health prior to pregnancy. This will be measured through the change in waist circumference after the 8-month intervention period between female subjects exposed to the intervention and female subjects exposed to standard of care in a control group. The secondary objectives are to evaluate the efficacy of the intervention on health literacy, dietary habits, physical activity, sedentary behaviour and stress level.

### Study design

The trial is designed as an unblinded, RCT to assess the efficacy of a complex behavioural change intervention aiming to improve the overall health of young women prior to their first pregnancy. The intervention follow-up period is 8 months from randomisation/baseline. After end trial the subjects will be monitored for a period of 12 months for pregnancy. Figure 1 gives the flow diagram of the trial. The trial was designed following the Standard Protocol Items: Recommendations for Interventional Trials (SPIRIT) 2013 statement (see Additional file 1).

**Fig. 1 Fig1:**
[figure not shown]
The flow diagram of the Jom Mama trial

### Site and participation selection

The trial will be carried out in the district of Seremban in the state of Negeri Sembilan, Malaysia. This location was selected due to Negeri Sembilan having a higher prevalence of diabetes (22.0 %) compared to the national prevalence (15.2 %) [22]. Ethnic diversity is one of the key features of Malaysia and the district of Seremban has a representation of the three major ethnic groups: Malay, Chinese and Indian, 67.4, 24.6 and 7.3 %, respectively [23].

The target subjects will be newly registered married or engaged women. The woman will be recruited with her spouse, who also will be exposed to the intervention.

### Inclusion and exclusion criteria

Eligible subjects must meet all the following inclusion criteria:Female and between the ages of 20–39 yearsNulliparousNot pregnant at the time of signing the informed consentOwn a smartphone, with either an Android operating system version 4.1 and above or iOS operating system 7.0 and above, and have Internet access

Subjects meeting any of the following criteria will be excluded from participation in the trial:Female subject undergoing treatment for type 1 or 2 diabetes mellitusSubject not residing in the district of Seremban

### Screening

Newly married or engaged women and their spouses will be recruited from 2 November 2015, primarily from five designated primary health clinics in the district of Seremban, whereas Muslim Malay couples are obligated to conduct a pre-marriage screening, which involves a HIV/AIDS test. Other sites in Seremban such as the state marriage registration office, temples and churches or other sites (work places, malls, gyms, etc.) will also be approached for recruitment purposes. A research officer will meet the young couples face-to-face and provide an explanation of the study rationale and a description of the Jom Mama project. The women and spouse will be given an opportunity to ask questions and those who are interested in the study will have their contact details recorded for further contact and arrangements for a baseline visit. If possible, the couple will be given a clinic appointment for baseline measurements at one of the five designated primary health clinics in Seremban. If the couple need time to consider their involvement, the research officer will follow-up with three phone calls over the next 3 weeks. If, at these phone calls the couple accepts participation in the trial, a baseline appointment will be made. If the couple does not answer the three phone calls or rejects the offer to participate, they will be dropped from the participation registration list.

### Intervention

The intervention has two components. The first component is an interaction with a CHP who will be in contact with the women and their spouses during the 8-month intervention period. These contacts will be a combination of three face-to-face meetings, three phone calls and communication through Whatsapp group chat. The CHP will use motivational counselling techniques, i.e. motivational interviewing, to support and motivate the young women and their spouses to live a healthier lifestyle. The second component is an E-health platform which consists of two elements: (1) a mobile application in the form of a habit formation application, where subjects and spouses can select different challenges for obtaining a healthy diet, more physical activity and less sedentary behaviour during the intervention period; and (2) a web-based back-end interface which can be accessed by the CHP, which will be her tool to assess the women and their spouses’ lifestyle situation. The CHP uses a dashboard to follow the progress of subject and spouse in performing the challenges, and uses the information to interact with the subject and her spouse during the contact points in the intervention. Figure 2 presents screen shots of the web-based application the CHPs are using. The CHP will function as a personal coach to engage, support and guide the young woman and her spouse toward achieving and maintaining a healthier lifestyle. During the interaction over the intervention period of 8 months, the CHPs will assess the subject and her spouse’s health risks and behaviour, share information on healthy living and support the subjects and spouses to reach their personal health goals. The objectives of each contact point are presented in Table 1.

**Fig. 2 Fig2:**
[figure not shown]
Screen shot from the web application, showing the couples’ dashboard. Screen shot **a** Shows the overview of all couples under one community health promoter (CHP). The traffic lights give an indication on how active the couple are in performing their selected challenges. The *second column* indicates when the couple was last active on the mobile application. The *last column* informs when the CHP has the next appointment with the couple. Screen shot **b** Shows the progress over time for one couple. The graphic can shift between wife and husband and, in this example, it is only showing the wife. The *upper columns* indicate how many times the challenges have been performed per month. The *lower columns* indicate how many times each challenge has been performed

**Table 1 Tab1:** Overview of the objective of each face-to-face and phone call contact point

Contact point	Objective
Contact point 1 (face-to-face)	Assessment of woman and spouse’s health risk and behaviour: conversation starter
	Introduce to use of mobile application
	Initiate review of assessments and behaviour change process
	Goal setting
Contact point 2 (face-to-face)	Follow-up on use of mobile application
	Provide health information as required
	Review and address extrinsic supportive and inhibiting factors
	Introduce proactive coping
Contact point 3 (phone)	Follow-up on use of mobile application
	Follow-up on progress based on initial goal setting
	Provide support and advice
	Provide health information as required
	Revise goal setting and set new goals as relevant
Contact point 4 (phone)	Follow-up on use of mobile application
	Follow-up on progress based on previously set goals
	Provide support and advice
	Provide health information as required
	Revise goal setting and set new goals as relevant
Contact point 5 (face-to-face)	Follow-up on use of mobile application
	Follow-up on progress based on previously set goals
	Provide support and advice
	Provide health information as required
	Revise goal setting and set new goals as relevant
Contact point 6 (phone)	Follow-up on progress based on previously set goals
	Provide support and advice
	Provide health information as required
	Goal setting and planning for the future
	End of intervention process

The CHP role will be carried out by community nurses who are currently working in primary health care in Malaysia. Prior to the start of the intervention, the community nurses undertook training in becoming a CHP. This was a 5-day training programme with sessions in motivational interviewing techniques, the use of the E-health platform and basic knowledge of healthy diet and physical activity. The training was carried out by local trainers who are social-psychologists with expertise in motivational interviewing techniques, professional dieticians and physical activity experts. During the trial, refreshment training with the social-psychologist trainers will take place to support and help the CHPs in addressing challenging situations they encountered with the young women and their spouses.

The mobile application is a habit-formation application, which incorporates personal goal setting, progress tracking and general information on healthy lifestyles. The mobile application has two key components comprising diet and physical activity. Under each domain several challenges have been developed which can be selected by the subject on a monthly basis in dialogue with the CHP. The application will suggest several challenges for healthy eating, such as making healthy food choices and healthy food preparation, and interactive options for the subject to stay active and prevent sedentary behaviour. In addition, the mobile application will also provide information on what constitutes a healthy lifestyle and further information on how to stay healthy before pregnancy. The mobile application is available on iOS and Android operating systems. Figure 3 presents several screen shots from the mobile application.

**Fig. 3 Fig3:**
[figure not shown]
Screen shots of mobile application. **a** The main screen, showing the couple’s process for the particular month. The icons on *top* illustrate the categories of the different challenges selected (two physical activity challenges and one healthy eating challenge). In the *middle*, is the progress bar, showing the progress of the user and her spouse for this particular month. *Lowest*, are the selected challenges listed and how many times they should be performed in one week. **b** By tapping on the challenges, a description of the different challenge is showing (example of the healthy eating challenge). **c** When the challenge has been performed, the subject will ‘check-in’, and by doing that be awarded 2 points for performing the challenges. **d** A timer can be set for each challenge, so a reminder will be send to the subject on the given time to perform the challenge. **e** The subject is selecting the challenge out of a list set challenges. **f** The Flash challenge is a bonus challenge, which the subject can select when it becomes available. This occurs randomly during the intervention period. The Flash challenge will give extra points

### Control arm

Subjects in the control arm will receive standard of care, which is no contact with a CHP and no access to the E-health platform. They will receive one phone call from a research officer towards the end of the intervention period to remind them of their endpoint visit.

### Outcomes

#### Primary endpoint

Change in waist circumference was selected as the primary endpoint because of its validity as a superior measurement for assessing abdominal fat content and associated obesity health risk, as compared to a measure such as body mass index (BMI) [24–26]. In addition, there are existing national Malaysian data on population waist circumference, which allow for the study results to be comparable on a national level. In the present trial, the primary endpoint is predicted to provide a 2-cm reduction of waist circumference in the intervention group compared to the control group, which will reflect a reduction of central fat distribution. The reduction of 2 cm in waist circumference as a primary endpoint is based on the mean from a number of studies indicating that a decrement of waist circumference is possible with a lifestyle changing intervention over a period of 8 months [27–31]. The variation between the two time-points in these studies was small (standard deviation (SD) of 3–5) after the intervention period, and we therefore assume an expected within-person estimate of SD = 5.

#### Secondary endpoints

The secondary endpoint will be as follows:Change in BMI from baseline to after 8 monthsChange in waist-to-height ratio from baseline to after 8 monthsChange in waist-to-hip ratio from baseline to after 8 monthsChange in weight from baseline to after 8 monthsChange in glycated haemoglobin A_1c_ (HbA_1c_) from baseline to after 8 monthsChange in the fasting lipid profile (total cholesterol, low-density lipoprotein cholesterol, high-density lipoprotein cholesterol and triglycerides) from baseline to after 8 monthsChange in blood pressure (systolic and diastolic blood pressure) from baseline to after 8 monthsChange in the level of health literacy, as measured by the European Health Literacy Survey Questionnaire (HLC-EU-Q47) from baseline to after 8 monthsChange in dietary intake, as measured by a Food Frequency Questionnaire (FFQ), from baseline to after 8 monthsChange in physical activity and sedentary behaviour, as measured by the International Physical Activity Questionnaire (IPAQ) used in national health surveys in Malaysia, from baseline to after 8 monthsChange in stress levels, as measured by the Depression Anxiety and Stress Scale 21-items (DASS-21) used by general practitioners in the Malaysian primary health care system from baseline to after 8 months

#### Other endpoints

The incidence of GDM, confirmed by an oral glucose tolerance test (OGTT), will be assessed in the subjects who will complete the intervention period and who become pregnant in the post-trial monitoring period. The OGTT will be taken at weeks 26–28 of the pregnancy. Data will be captured retrospectively and obtained from medical charts.

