#### Data collection

At baseline the subjects will undergo measurements of waist circumference, hip circumference, weight, height and blood pressure by following standardised procedures based on World Health Organisation (WHO) STEPS surveillance [32]. Only the subject in the couple will provide a 10-mL blood sample to measure glycated haemoglobin A_1c_ (HbA_1c_) and a fasting lipid profile (triglycerides (TG), low-density lipoprotein cholesterol (LDL-C), high-density lipoprotein cholesterol (HDL-C) and total cholesterol (TC)). Due to the need for a fasting lipid profile analysis, the subject will be asked to come to the clinic after fasting for a minimum of 9 h. In line with this, the data collection time-points are planned to be in the morning. The European Health Literacy Tool Q-47 (HL-EU-Q47) [33] (HL-EU Consortium 2012), the Malaysian Food Frequency Questionnaire (FFQ), modified to be used in the current trial [2]; the International Physical Activity Questionnaire (IPAQ) [2]; and the Depression Anxiety Stress Scale 21-items (DASS-21) [34, 35] will be used to collect data on level of health literacy, dietary pattern, physical activity level, and stress level, respectively. Data such as socio-demographic parameters and family history of diabetes will be collected by structured interviews with the study nurse. The spouse will undergo the same data measurements, with the exception of blood sampling. At the end of the data collection, and before subject and spouse leave, data will be checked by the study nurse and site coordinator or research officer, to ensure that all data forms and questionnaires have been filled correctly. When data collection is completed the data collection forms and questionnaires will be signed-off by the study nurse and site coordinator or research officer. At the end of the baseline visit, if the subject is randomised to the intervention, the first contact with a CHP will be made. The subject and spouse will be introduced to the mobile application and it will be installed on the subject’s and spouse’s smartphone device. If the subject and spouse have sufficient time the CHP will proceed with the first contact point. If the subject and spouse do not have the time, an appointment will be set in the next 5 days either at the clinic or at the couple’s house. The same measurements, except height, socio-demographic parameters and medical history, described above will be conducted at the endpoint visit (Table 2).

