#### Statistical analysis

The null hypothesis is that there is no difference in the change in waist circumference between the intervention and the control group after the 8-month intervention. The alternative hypothesis is that the decrement in waist circumference will be bigger in the intervention group compared to the control group after the 8-month intervention. A linear regression model will be used to assess the difference in the change of waist circumference from baseline to end of intervention, with the difference in waist circumference as the independent variable, treatment (intervention versus control) and baseline waist circumference as covariates. Additional tests will be performed for the impact of the intervention in both high- (waist circumference above 80 cm) and low-risk (waist circumference below 80 cm) groups. This will be done by subgroup analysis or by assessing the proportional changes in the primary endpoint. Each subgroup will also be analysed in a linear regression model. The continuous secondary endpoints will be analysed in a linear regression model, whereas the difference in the change of each secondary endpoint from baseline to end of intervention, will be the dependent variable, treatment (intervention versus control) and baseline value as covariate. Regarding health literacy (HL-EU-Q47), physical activity (IPAQ) and stress (DASS-21) all the variables are ordinal and, therefore, independence between intervention and control groups will be tested with the chi-squared test. Change in nutrient intakes will be compared between the groups using a generalised linear model, with additional adjustments for total energy intake. Nutrient and food patterns before and after the intervention will be explored in both groups separately by using dimension reduction techniques such as principal component analysis. Multivariate analysis will be performed to assess the association between exposure to the intervention, primary endpoints and secondary endpoints (BMI, waist-to-height and waist-to-hip ratio, HbA_1c_, lipid profile, blood pressure, health literacy, physical activity, dietary intake and stress level) using linear regressions. In this model the secondary endpoint will be included in the model as covariates and the estimated coefficients will be presented unadjusted and adjusted for appropriate and/or effect modifier and/or confounders. Furthermore, interactions between the secondary endpoints will also be explored. Several supportive analyses will be performed. The first supportive analysis will explore the relation between subjects’ and spouses’ change in waist circumference and other anthropometric measurements, diet, physical activity, health literacy and stress. A second supportive analysis will explore whether a short intervention period (subjects who become pregnant between 4.1 and 8 months in the intervention period), will also have an impact on the primary endpoint and secondary endpoints. A time variable explaining how long they have been included in the intervention will be included in the models as a covariate. At the end of the 12-month post-intervention monitoring period, a full analysis will be conducted on subjects who become pregnant within 12 months after completing the intervention. This will be done by assessing the incidences of GDM among women who became pregnant between treatment groups, using a chi-squared test. Additionally, a logistic regression model to explore associations between the number of subjects with GDM and several secondary endpoints will be conducted.

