#### Safety monitoring

In the event of an abnormal laboratory test results for Hb1Ac or a newly suspected or diagnosed health concern during a subject’s measurements (i.e. high blood pressure or a high score in the DASS-21 tool) at baseline/exit point/endpoint, the subject will be referred to their primary health care physician for further examination.

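### The GDM comparison takes all completers who become pregnant as its risk set and states no rule separating diabetes that predates pregnancy, although the entry criteria admit such women

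*Protocol article*

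**What the plan says.** **Endpoint.** Under Other endpoints, the protocol article states: "The incidence of GDM, confirmed by an oral glucose tolerance test (OGTT), will be assessed in the subjects who will complete the intervention period". The population is further limited to women with a pregnancy during post-trial monitoring, which lasts 12 months. On timing and source it says "The OGTT will be taken at weeks 26–28 of the pregnancy" and "Data will be captured retrospectively and obtained from medical charts".

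**Analysis.** The Statistical analysis section describes "assessing the incidences of GDM among women who became pregnant between treatment groups, using a chi-squared test". It also plans a logistic model relating GDM to several secondary endpoints, which it does not name.

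**Entry.** The abstract describes eligible women as those "who are nulliparous, not diagnosed with diabetes and own a smartphone". The Inclusion and exclusion criteria section instead excludes only women who are being treated for type 1 or type 2 diabetes. No HbA1c or glucose limit applies at entry.

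**Glycaemia data.** The Data collection section says "Only the subject in the couple will provide a 10-mL blood sample to measure glycated haemoglobin A_1c_ (HbA_1c_) and a fasting lipid profile". This happens at baseline, the visit at which women are randomised, and again at the endpoint visit. Safety monitoring covers what follows: "In the event of an abnormal laboratory test results for Hb1Ac", or another newly suspected health concern at a measurement visit, "the subject will be referred to their primary health care physician for further examination". Neither withdrawal nor separate classification for the GDM analysis is mentioned.

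**The concern.** Incidence needs a denominator of women who could become new cases. A woman who already has diabetes at conception cannot develop GDM as a new condition. An OGTT at weeks 26–28 alone does not show whether the raised glucose began before the pregnancy.

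The article names the population, the test, its timing, the data source and the comparison. None of these takes such women out. One of them can enter the comparison wrongly in two ways:

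- as a case, if her chart records GDM on the strength of the OGTT;
- as a non-case, if her diabetes is already known and no OGTT is done.

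At stake is the size of the GDM risk ratio in a small subset, where a few misplaced women count. The trial already collects the measurement that would identify most of them before pregnancy, but the stated analysis does not use it.

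**Working it through.** **The plan's own figures.** The only sample size concerns waist circumference: 2 × (1.960 + 1.282)² × 5² / 2² = 131.4, so 132 per arm and 264 completers, as stated. The article gives no GDM rate, effect or power, so there is no GDM figure to reproduce.

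**Who can be enrolled**

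| Woman at entry | Abstract wording | Criteria section |
|---|---|---|
| Treated diabetes | out | out |
| Diagnosed, untreated | out | in |
| Undiagnosed | in | in |

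The two texts disagree on the second row. Both admit the third.

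**How many pregnancies.** The sample size section allows for 20% pregnant, taken here as over the 8-month period. Assuming a constant rate, 12 months gives 1 − 0.80^1.5 = 0.284, and 264 × 0.284 ≈ 75 women over both arms.

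**Share affected, q.** The documents give no figure for women aged 20–39. The Background figures give 17.5% × 46.3% = 8.1% (Malaysian adults; worldwide undiagnosed share). The state prevalence under Site and participation selection gives 22.0% × 46.3% = 10.2%. Both are all-adult figures and serve as a rough ceiling, not an estimate. I use 2%, 5% and 8%, which is 1.5, 3.8 and 6 of 75 women.

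**Effect if every affected woman is charted as GDM.** Assume a true control risk g = 15% and a true risk ratio of 0.50 (neither is in the documents), with the same q in both arms.

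Observed risk: control = q + (1 − q) × 0.15; intervention = q + (1 − q) × 0.075.

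| q | Control | Intervention | Risk ratio | Difference (points) | Pre-existing share of control cases |
|---|---|---|---|---|---|
| 0 | 15.0% | 7.5% | 0.50 | 7.5 | 0 |
| 2% | 16.7% | 9.35% | 0.56 | 7.35 | 12% |
| 5% | 19.25% | 12.1% | 0.63 | 7.1 | 26% |
| 8% | 21.8% | 14.9% | 0.68 | 6.9 | 37% |

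**Effect if none is charted as GDM.** Both risks are multiplied by (1 − q), so the ratio stays at 0.50.

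**In between.** If a fraction f is charted as GDM, each risk is q × f + (1 − q) × true risk. With q = 5% and f = 0.5: control 0.025 + 0.1425 = 16.75%, intervention 0.025 + 0.07125 = 9.6%, ratio 0.57. The term q × f cancels in the difference, which is (1 − q) times the true one whatever f is.

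**Power.** Take an assumed 20% versus 12% and 66 pregnant women per arm, which is half of all completers and more than the estimate above. At q = 5%, power is 19.0% with pre-existing cases scored as GDM and 22.9% with them removed.

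**The case against.** The article does not say that any positive OGTT counts as GDM. A reader might infer this, but the text speaks of GDM confirmed by an OGTT and taken from charts, and a clinician may well have charted known diabetes as such. That stands: the documents support only that no separating rule is stated, and the ratios tabulated for all affected women charted as GDM are upper bounds for each q.

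HbA1c is measured at baseline and at 8 months, and abnormal results lead to referral. Because the GDM population is limited to completers, many affected women should be known before they conceive. That also stands. It lowers the number charted as GDM. It does not take known cases out of the denominator.

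Case definitions for a lesser endpoint are often left to the full protocol or analysis plan, neither of which is shown. This has weight for diagnostic thresholds, whose absence I do not criticise. It has less weight for the risk set, which the article does state, and none for the conflict between the abstract and the criteria section.

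A reader might also infer that the logistic model builds in an association between HbA1c and GDM. The documents do not support this: the model's covariates are not named, and the listed secondary endpoint is change in HbA1c, not its level.

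Finally, GDM is listed among other endpoints, has no power calculation, and would be underpowered in the scenario above whether or not these women are removed. That stands and limits the severity.

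**Conclusion.** The point holds as a minor one. The stated GDM risk set includes women who cannot become incident cases, and the entry rules let them in. The bias in the risk ratio is towards no effect and depends on how many of these women are charted as GDM. A true ratio of 0.50 would appear as at most 0.56 at q = 2% and 0.63 at q = 5%, and would not move if none were so charted. The absolute difference loses only the fraction q of its size.

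These sizes rest on an assumed 15% control risk, an assumed true ratio of 0.50, equal q in both arms, and a q that the documents do not give. They do not show that the GDM result will be materially wrong, and the primary endpoint is unaffected.

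**What to change.** - Define the main GDM risk set as women who become pregnant in the monitoring period, had no known diabetes at randomisation, and had a baseline HbA1c below the diabetes diagnostic range used by the study laboratory. Use the baseline value, not the 8-month one, because the intervention may change the latter.
- Report pre-existing diabetes as a separate category, by arm.
- Keep the comparison among all pregnant completers as a sensitivity analysis.
- Reconcile the diabetes wording in the abstract with that in the Inclusion and exclusion criteria section.

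The cost is a sentence or two in the endpoint definition and analysis text. No new sampling is needed, because baseline HbA1c is already collected from every woman. The main comparison loses a few women, about 1.5 to 6 of 75 under the assumptions above.
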